### Recruitment

Recruitment will take place in the PHCs. Medical Officers will be requested to direct adults attending the outpatient department to the PRS stationed at these PHCs. PRS will check eligibility before obtaining written informed consent and contact details for enrolment. We will target 70–80 participants per month per PHC to recruit 300 participants from each PHC. Awareness campaigns will be carried by distributing study brochures, posters within the PHC, conducting community meetings to achieve desired recruitment.

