**Methods:**

Formative phase will involve qualitative interviews, literature review aimed at co-developing a mobile application with the district mental health program. This will be followed by a cRCT. The trial will be conducted in eight PHCs, located in Tumkur district, Karnataka, and Wardha district, Maharashtra. Randomisation will be done at the PHC level. We plan to enrol non-specialist HWs working in these PHCs and a sample of 2400 adults who are availing the PHC services. Intervention PHC will receive training for HWs and a mobile application. Control PHCs will follow usual care. Both the groups will be encouraged to identify, manage, and follow-up people with mild depression. Study tools include PHQ-2, PHQ-9, acceptability of intervention measure, and Eq. 5D5L instrument. Change in the detection rates of depression between intervention and control arms will be the primary outcome. Cost effectiveness analysis will be done.

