### Study setting

The trial will be conducted in eight PHCs, located in Tumkur district, Karnataka, and Wardha district, Maharashtra. Tumkur district has ten administrative sub-divisions and 150 PHCs, while Wardha district has eight sub-divisions and 33 PHCs. The PHCs are located between 30 and 100 km from the study sites. PHCs will be ranked based on the criteria given in Table 1. The top 20 ranked PHCs will be listed in descending order, and four PHCs will be randomly selected from each site.

**Table 1 Tab1:** Criteria for selection of PHCs

PHC selection criteria	Ranking based on
*1. Distance from the study site to the PHC*	Farther less score
*2. Population catered by the PHC*	≥ 30,000 higher score
*3. Number of HWs working in the PHC*	≥ 10 higher score
*4. Monthly footfall of adult patients in the PHC*	≥ 2000 higher score
*5.Ongoing mental health research in the PHC*	Absent more score

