**Fig. 2 Fig2:**
[figure not shown]
Consort flow diagram

Phase I: In this, baseline data collection using outpatient records in all study PHCs will be carried out to determine the PHC footfall, number of adults diagnosed, managed, or referred for mental health conditions over the past six months.

Phase II: PHCs will be randomised and allocated into the intervention arm (*n* = 4) and the control arm (*n* = 4). Subsequently, intervention package will be delivered to HWs in the intervention PHCs. HWs at the control PHCs will receive a one-day sensitisation session on mental health conditions, including brief psychoeducational counselling on depression.

Phase III: Screening, assessment, psychological counselling of adult participants by HWs, and referrals will take place during this phase. In both intervention and control PHCs, adults attending the study PHCs will be enrolled consecutively ss per the eligibility criteria. They will be allotted to each HW depending on the availability of HW in the PHCs for screening, assessment, and management of depression.

Phase IV: In both arms, participants identified with mild depression will receive psychological counselling from HWs and will be followed up as outlined in the pilot phase. Each follow-up counselling session will last 10 min per participant. PRS will give telephonic reminders to participants to reduce dropouts. Screening, assessment, and management of mild depression will be done using application in intervention PHCs and through usual care in control PHCs by the HW.

Validation by PRS: At the time of baseline assessment, the PRS will validate all participants identified with mild depression by HWs. Along with this, PRS will also randomly conduct a validation check PHQ 9 scores in participants identified as normal by HWs. To document changes in PHQ-9 scores, the PRS will administer the PHQ-9 to participants at all follow-up visits. PRS will do a health-related quality of life (HRQoL) assessment at baseline and the last follow-up.

Referral: Participants with PHQ-9 scores ≥ 10 or having suicidal ideation will be referred to the DMHP psychiatrist at the sub-district hospital. The PRS will contact participants telephonically to ensure they receive appropriate care. Throughout the study, the research team will provide weekly supportive supervision to all HWs in both arms to provide feedback and address any issues they may face.

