### Participant timeline

The participant timeline has been presented in Table 4.

**Table 4 Tab4:** Participant timeline

	Year 1				Year 2				Year 3			
Project activities	1	2	3	4	1	2	3	4	1	2	3	4
Administrative permissions	X											
Development of mobile application		X	X	X								
Development of training modules			X	X								
Pre-trial pilot phase												
Pilot study				X	X							
Trial phase												
Selection of PHCs					X							
Recruitment of HWs					X							
Baseline data collection					X	X						
Randomisation						X						
Delivery of intervention						X	X	X				
Recruitment of adult participants							X					
Screening and counselling by HWs							X	X	X			
Follow-ups and outcome assessments							X	X	X	X		
Post-trail phase												
Measurement of costs							X	X	X	X		
Acceptability & feasibility measures										X		
Analysis, & report preparation									X	X	X	X
Project conclusion												X

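### Adults are recruited after PHC allocation by staff who know the arm, and no stated rule secures consecutive enrolment, so case mix may differ by arm

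*Protocol article*

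**What the plan says.** All references are to the protocol article.

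- **Order of events.** Implementation puts allocation first ("Phase II: PHCs will be randomised and allocated into the intervention arm"), followed by delivery of the package to health workers in the same phase. Adults enter in Phase III. Table 4 (Participant timeline) agrees: randomisation is in Year 2, quarter 2, and the row "Recruitment of adult participants" is marked in Year 2, quarter 3.
- **Stated sampling.** Implementation, Phase III, says "adults attending the study PHCs will be enrolled consecutively" in both arms, subject to eligibility.
- **Route into the trial.** Recruitment says "Medical Officers will be requested to direct adults attending the outpatient department to the PRS stationed at these PHCs". Brochures, posters and community meetings are added to reach the target. The PRS checks eligibility and takes consent.
- **Pace.** "We will target 70–80 participants per month per PHC to recruit 300 participants from each PHC".
- **PHC size.** Table 1 (Study setting) lists "Monthly footfall of adult patients in the PHC" as a ranking criterion, with a higher score at 2,000 or more.
- **Blinding.** The Blinding section rules it out for health workers and claims none for Medical Officers or the PRS. Under Data collection methods, PRS validation data go into the app in one arm and onto a paper form in the other.
- **Outcome.** The abstract says "Change in the detection rates of depression between intervention and control arms will be the primary outcome".

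**The concern.** In a cluster trial, randomising PHCs protects against imbalance in who is enrolled only if adults are identified before allocation, or by a process that allocation cannot influence. Neither is assured here. Adults are identified after allocation, the first step runs through a Medical Officer, and the person taking consent knows the arm. Publicity brings in people who respond to the study, which is not the same as taking attenders in sequence.

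The primary outcome is sensitive to this. If detection is the number of adults detected divided by the number enrolled, an arm that enrols more depressed adults detects more of them even when its health workers are no better at detection. The GEE model under Statistical methods is specified to adjust for cluster effects. That does not remove a case-mix shift that runs along with the arm.

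**Working it through.** The plan gives no figure on this point to reproduce. The check has three steps.

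**1. Do the passages secure consecutive enrolment?** Implementation names consecutive enrolment. Recruitment names two mechanisms, Medical Officer direction and publicity. It does not require that every attender be sent, and it describes no record of those not sent. The aim is stated, but the mechanism does not guarantee it.

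**2. How many attenders enter?** At the Table 1 threshold of 2,000 adults a month, 70/2,000 = 3.5% and 80/2,000 = 4.0%. The threshold is a scoring criterion, and the count precedes eligibility exclusions. If only 20% of attenders were eligible (assumption), there would be 400 a month, and 70/400 = 17.5% to 80/400 = 20% of them would enter. Under these figures, something other than eligibility decides who enters. Health-worker availability may be part of it.

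**3. What could a case-mix shift do?** Assume no intervention effect, equal sensitivity in both arms, only true cases counted, neutral enrolment in control PHCs, and detection counted per enrolled adult. Sample size supports the last assumption, since it applies 5% and a 20% difference (read as 5% v 25%) to 300 adults per PHC and 1,200 per arm.

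- Prevalence odds among those enrolled = prevalence odds among attenders × odds ratio of being sent (a good approximation when a small fraction enters).
- Spurious difference = sensitivity × (prevalence enrolled, intervention − prevalence enrolled, control).

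At an assumed prevalence of 20% the odds are 0.20/0.80 = 0.25.

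- Odds ratio 2: 0.25 × 2 = 0.50, and 0.50/1.50 = 33.3%. The shift is 13.3 points; × 0.5 = 6.7 and × 0.8 = 10.7 points.
- Odds ratio 1.5: 0.25 × 1.5 = 0.375, and 0.375/1.375 = 27.3%. The shift is 7.3 points; × 0.5 = 3.6 and × 0.8 = 5.8 points.

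The same formulas over a range of assumed prevalence:

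| Prevalence among attenders | Odds ratio | Prevalence among enrolled | Shift (points) | Spurious difference, sensitivity 0.5 to 0.8 (points) |
|---|---|---|---|---|
| 10% | 1.5 | 14.3% | 4.3 | 2.1 to 3.4 |
| 10% | 2 | 18.2% | 8.2 | 4.1 to 6.5 |
| 20% | 1.5 | 27.3% | 7.3 | 3.6 to 5.8 |
| 20% | 2 | 33.3% | 13.3 | 6.7 to 10.7 |
| 30% | 1.5 | 39.1% | 9.1 | 4.6 to 7.3 |
| 30% | 2 | 46.2% | 16.2 | 8.1 to 12.9 |

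Lower sensitivity shrinks the difference. If 5% detection and 20% prevalence both hold, sensitivity is 0.05/0.20 = 0.25, and the spurious difference is 0.25 × 13.3 = 3.3 points at odds ratio 2 and 0.25 × 7.3 = 1.8 points at 1.5. On the ratio scale of the log-link model, sensitivity cancels: at 20% prevalence the spurious ratio is 33.3/20 = 1.67 or 27.3/20 = 1.36, against a planned 25/5 = 5.

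**The case against.** A reader might infer that Medical Officers choose whom to send, so that Recruitment flatly contradicts consecutive enrolment. The text does not support this. Medical Officers are asked to direct attenders, selection is not mentioned, and they could direct everyone while the PRS enrols eligible adults in sequence. The publicity is the clearer tension.

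Nor does the 3.5% to 4% figure prove selection. PHCs below the footfall threshold can be drawn, and the eligibility criteria exclude adults over 60, acute illness, pregnancy, lactation and known psychiatric conditions. Adults are also allotted according to health-worker availability.

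The mechanism is possible but not shown. Training is for health workers, and no passage trains Medical Officers in either arm. That they know the arm is an inference, though a reasonable one when their own staff receive a three-day course and an app. Control health workers are sensitised too, and both arms share one route and weekly supervision.

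It is also tempting to set the 13-point prevalence shift directly against the planned 20 points. These are different quantities, because sensitivity must be applied first. The denominator is not settled either. Sample size cites the same sources for its 5% as the Background does for the large share of undetected cases, which may mean detection among cases. On that reading a prevalence shift does not directly inflate the outcome.

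Finally, the PRS re-checks PHQ-9 in some adults rated normal, and the DSMB reviews enrolment procedures. These may reveal an imbalance, but they do not prevent one, and the PRS is not blinded.

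What stands after all this is the order of events, the PRS's knowledge of the arm, and the absence of a rule that secures consecutive enrolment.

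**Conclusion.** The concern holds as a design weakness that should be corrected. Recruitment follows allocation, is run by staff who are not stated to be blinded, and uses a route that does not secure the sampling promised elsewhere in the same article. Case mix may therefore differ by arm; the documents do not show that it will.

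In the central illustration, the spurious difference is about 7 to 11 points at odds ratio 2 and 4 to 6 points at odds ratio 1.5. That is roughly one-sixth to one-half of the planned 20 points, and less if sensitivity is lower. These sizes rest on assumed prevalence, sensitivity and odds ratios, and on a per-enrolled-adult denominator. The inputs do not describe the planned effect itself: 25% detection per enrolled adult cannot arise from 20% prevalence without false positives. The figures show what is possible and are not a forecast.

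**What to change.** 1. In Recruitment, replace Medical Officer direction with selection by the PRS from the outpatient register under one fixed rule in all eight PHCs, for example every k-th eligible attender, with k set from the Phase I footfall. Align the Phase III wording with this rule.
2. Use identical, neutral brochures, posters and meeting content in both arms, and enrol nobody outside the register rule.
3. Keep a log per PHC of adults approached, eligible and consented. The PRS will still know the arm, so the log is what would show differences in approach or consent.
4. Compare PRS-measured PHQ-9 prevalence by arm. Because only a random part of the adults rated normal is re-checked, weight these by the inverse of their sampling fraction, and include those scoring 10 or more.

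Cost: a slightly slower approach at the PHC and some extra logging by PRS staff already in post. Steps 1 and 2 work only prospectively, since a difference in who was enrolled cannot be undone afterwards.

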### Data collection methods

Qualitative interviews will be conducted using IDI and FGD guides, prepared by the research team. Pre-training and post-training knowledge of HWs will be assessed using mhGAP knowledge questionnaire [44]. 

Screening and assessment of participants will be done using the PHQ-2 and PHQ-9. PHQ-2 has been recommended as a pre-screen prior to administering PHQ-9 items [45]. A score of ≥ 3 requires further assessment with PHQ-9 to determine severity of depression. The PHQ-9, designed for primary care settings, consists of 9 items which measure the frequency of depressive symptoms over the past fortnight. A multicentric Indian study reported PHQ-9 reliable for screening depression by HWs [46]. Table 5 provides the operational definitions of our study.Acceptability and feasibility of the intervention will be assessed using AIM instrument [47]. 

The HRQoL will be measured at baseline and endline by the PRS using EUROQUAL instrument (EQ-5D-5 L), the norms of which are available for the Indian population [48]. 

Detailed costing of every single ingredient will be gathered for doing cost-effectiveness analysis.

**Table 5 Tab5:** Operational definition for PHQ-9 used in the study

Operational definition	PHQ-9 score
*1. Normal*	< 5
*2. Mild depression*	5–9
*3. Moderate depression*	≥ 10
*4. Severe depression*	≥ 15
*5. Recovery*	< 5

The socio-demographic details from participants will be used to generate a unique identification number (UID).

In the intervention arm, screening, assessment, and counselling of participants by HWs, validation by the PRS and follow-up data will be captured in the mobile application. This data will get stored in the application backend which can be downloaded in Microsoft Excel format. In the control arm, screening, assessment, follow-up, and validation data will be captured using a case record form (CRF). This along with the HWs knowledge scores, EQ-5D-5 L scores, AIM scores, and costing data will be collected using Epicollect5 with appropriate quality checks to minimise errors. Respective site PIs will constantly monitor all the data captured through the application and by Epicollect5.

### Plans to promote participant retention and complete follow-up

Strategies to minimise loss to follow-up will include using simplified application usage to reduce the burden on HWs, flexibility in scheduling follow-ups, and periodic telephonic reminders to adult participants. Regular weekly meetings with the HWs will be held for supportive supervision and to address their concerns. Details of drop-outs or participants lost to follow-up will be documented appropriately.

### Ethical data management

Research team will be trained in collecting data under strict confidentiality, using standard study tools. Consent forms and CRF will be appropriately stored, ensuring protection from damage, fire accidents, or theft by locking them in a designated, secure office. All data with demographic details will be delinked from the indirect identifiers. Before delinking, the master sheet that links the participant’s name and phone numbers linked to their UID will be securely stored in a password-protected computer accessible only to PIs. A Data and Safety Monitoring Board (DSMB) will be constituted to monitor and audit the conduct of the research.

### Statistical methods

The qualitative data will be audio-recorded and transcribed verbatim. The transcriptions and the field notes from IDIs and FGDs will be manually coded. An inductive-deductive approach will be used to identify key themes and sub-themes. Reporting will be done using the Consolidated Criteria for Reporting Qualitative Studies (COREQ) checklist [49]. 

After checking for normality, continuous data will be expressed using mean (standard deviation) or median (interquartile range). Categorical data will be described using frequency and percentages. The difference in the detection and recovery rates between intervention and control arms, as well as associated risk factors for depression, will be compared using generalised estimating equation (GEE) analysis with a log link and exchangeable correlation structure to adjust for cluster effects. The change in EQ-5D-5 L scores during the follow-up will be compared between two groups using a mixed linear model. A p-value less than 0.05 will be considered significant. Missing data will be handled using multiple imputation methods.

Standard health economic methods will be applied to determine the incremental cost-effectiveness ratio (ICER) based on the costs and outcomes associated with the intervention. Sensitivity analyses will be conducted to test the robustness of the results. All analyses will be carried out using R software. Tree age software will be used to perform cost-effectiveness analyses.

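### Recovery is compared between groups formed after randomisation by the detection process under test, and an unconfirmed case could count as recovered

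*Protocol article*

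**What the plan says.** Under Implementation, Phase II, "PHCs will be randomised and allocated into the intervention arm" or the control arm. HWs screen adults afterwards, in Phase III. Phase IV says that screening, assessment and management are done "using application in intervention PHCs and through usual care in control PHCs".

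Phase IV also says who is followed: in both arms, "participants identified with mild depression will receive psychological counselling from HWs and will be followed up". No follow-up is described for adults whom the HW classed as normal.

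Under Validation by PRS, at baseline "the PRS will validate all participants identified with mild depression by HWs", and "PRS will also randomly conduct a validation check PHQ 9 scores in participants identified as normal by HWs". Later, "the PRS will administer the PHQ-9 to participants at all follow-up visits".

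Table 5 gives Normal and Recovery the same definition, a PHQ-9 score below 5, and defines mild depression as 5 to 9.

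Statistical methods then compares "The difference in the detection and recovery rates between intervention and control arms" by GEE with a log link and an exchangeable correlation structure to account for clustering. It names no denominator for recovery.

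**The concern.** Detection is the primary outcome, and the sample size assumes that it differs between arms. Recovery can be measured only in people who have been detected. Membership of the recovery denominator is thus itself an effect of allocation, and the people in it may differ between arms in severity and in whether they had mild depression at all. GEE handles the correlation within PHCs and multiple imputation handles missing scores. Neither corrects for this selection.

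The shared cut-off adds a second route. Someone whom the HW labels as mild but who truly scores below 5 meets the recovery definition from the start. If such people stay in the denominator, the recovery rate partly measures labelling accuracy.

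The stake is the claim about management. Management stands beside detection in the second primary objective, and recovery has its own sample-size calculation. A difference produced by who was labelled could be read as better counselling, or a real benefit could be diluted.

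**Working it through.** **The plan's own recovery figure.** Inputs from Sample size: 54% recovery under usual care, a difference of 20% (read as absolute, so 74%), 80% power, two-sided 5% alpha. With pooled variance, the mean proportion is 0.64 and

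n = [1.960 × √(2 × 0.64 × 0.36) + 0.842 × √(0.54 × 0.46 + 0.74 × 0.26)]² / 0.20² = (1.330 + 0.559)² / 0.04 ≈ 89.2 per arm.

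This rounds up to 90 and matches the stated 89. The calculation treats the two recovery groups as simple independent samples.

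**How the groups form.** Inputs from Sample size: 5% detection, a difference of 20% (again read as absolute, which the text does not state), 1200 adults per arm.

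- Control: 1200 × 0.05 = 60 detected.
- Intervention: 1200 × 0.25 = 300 detected.

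If the trial works as planned on this reading, the recovery groups differ fivefold in size through the effect of the intervention itself.

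**False positives, no true effect on recovery.** Let f be the share of false positives among those followed and q the chance that a false positive scores below 5 at follow-up. The documents give neither, so both are assumptions. True cases recover at 54% in both arms.

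Observed recovery = (1 − f) × 0.54 + f × q

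The spurious difference is therefore (gap in f) × (q − 0.54). With q = 0.90:

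| f in one arm | f in the other | Observed recovery | Difference |
|---|---|---|---|
| 40% | 10% | 68.4% v 57.6% | 10.8 points |
| 30% | 10% | 64.8% v 57.6% | 7.2 points |
| 20% | 5% | 61.2% v 55.8% | 5.4 points |
| 20% | 20% | 61.2% v 61.2% | 0 |

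Swapping the arms reverses the sign. With q = 1, shares of 30% v 10% give 67.8% v 58.6%, or 9.2 points. Reproducing the whole planned 20 points would need a gap of 0.20 / 0.46, about 43 points, with q = 1, or 0.20 / 0.36, about 56 points, with q = 0.90.

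**Equal false-positive shares, true effect of 20 points.** With f = 20% in both arms, the observed difference is 0.8 × 20 = 16 points. Taking q = 1 (63.2% v 79.2%), power at 89 per arm falls from about 80% to about 66%.

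**Case mix with no false positives.** Assume confirmed cases near the cut-off recover at 70% and the rest at 45% in both arms. If the near group makes up 30% of one arm and 60% of the other:

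- 0.30 × 0.70 + 0.70 × 0.45 = 52.5%
- 0.60 × 0.70 + 0.40 × 0.45 = 60.0%

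That is 7.5 points with no treatment effect. Excluding false positives alone does not remove the selection, which is why baseline adjustment and honest labelling are also needed.

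**The case against.** The strongest reply is that the PRS validates every HW-identified mild case at baseline and scores every follow-up visit, so the material to remove false positives is already planned. The article does not say that unconfirmed cases are kept, and analysis sets and covariates are often left to a fuller document. A common cut-off below 5 is no error in itself: among confirmed scores of 5 to 9 it properly separates recovered from not recovered.

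Much of this stands. The validation is a real safeguard, and the false-positive route matters only if unconfirmed cases stay in the comparison. Silence on covariates alone would be no finding. What remains is fixed in this article: who is followed up, when and by what process they are identified, and what counts as recovery. Together these make the stated comparison one between groups selected after randomisation, even when every case is confirmed.

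A reader might infer that the arm labelling more people must hold more borderline or wrongly labelled ones, so that the bias favours the intervention. The documents do not support this. Intervention HWs receive three days of training, a refresher and PHQ-2 and PHQ-9 within the application, against one day of sensitisation for controls. Their false-positive share could be the lower one.

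A reader might also infer that the artefact passes into the cost-effectiveness result. The article does not name recovery as the effect measure of the ICER, so that link is not established. Recovery is also not listed among the outcomes in Table 3.

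**Conclusion.** The point holds as a risk of bias of unknown direction. It does not show that the comparison is biased in a known way. Followed as written, the recovery analysis contrasts groups formed after randomisation by the process under test, adjusts only for clustering, and allows a false positive to count as recovered.

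The restriction to detected adults is inferred from the follow-up design, since Statistical methods states no denominator. The size of 5.4 to 10.8 points for a 15 to 30 point gap in false-positive share is an illustration. It rests on 54% true recovery in both arms (the plan's usual-care figure) and on assumed false-positive shares and an assumed 90% below the cut-off. Equal shares give dilution and no spurious difference.

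The same caution applies to change in EQ-5D-5L if it is measured only in participants who are followed up. The article places that assessment at baseline and the last follow-up but does not say in whom. The primary detection comparison is not touched by this point.

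**What to change.** 1. Restrict the recovery and PHQ-9 change analyses to participants with a PRS-confirmed baseline PHQ-9 of 5 to 9, use PRS scores only, and adjust for the PRS baseline PHQ-9. This defines an analysis set and does not alter whom the HWs counsel or follow.
2. State that the PRS validation of HW positives is recorded as a PHQ-9 score. The article mentions the PHQ-9 explicitly only for the check on those classed as normal.
3. Report the number and share of HW positives not confirmed, by arm.
4. Describe the result as a comparison of groups selected after randomisation, not as a randomised effect on management. Confirmation and adjustment reduce the selection problem but do not remove it.
5. As a supporting outcome only, report the proportion of all enrolled adults who were detected, PRS-confirmed and recovered, by arm. State that it combines detection with recovery and rises with detection alone: with 54% recovery in both arms and all detected cases confirmed, 5% v 25% detection gives 0.05 × 0.54 = 2.7% v 0.25 × 0.54 = 13.5%. It cannot answer the management question by itself. Adults are also enrolled after the PHCs are randomised, so even this denominator is not immune to differential recruitment.
6. Say in whom EQ-5D-5L is measured at the last follow-up. If only in followed participants, apply the same labelling.

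The cost is mainly wording, since PRS baseline validation and follow-up scores are already planned. The downside is a smaller recovery denominator, which matters most in the control arm, where the plan's own rates imply about 60 detected adults before any exclusion, against the 89 required.

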### Sample size

The sample size was calculated by considering a 5% detection rate of depression at primary care level [9, 10] and assuming a difference in detection rate by 20% between the intervention and control arm. Assuming an equal cluster size of 300, we will require 4 PHCs in each arm. Considering 20% attrition rate, intra-class correlation (ICC) as 0.1 [43], with 80% power, 5% alpha error for two-sided test, the minimum sample size required is 1200 adults per arm. Assuming the usual recovery rate for depression at the primary level to be 54% and an expected difference of 20% in the recovery rates between intervention and control arms, with 80% power, 5% alpha error for two-sided test, the required estimated sample size is 89 patients in each arm. Therefore, a minimum of 1200 participants per arm will be sufficient.

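### The trial is sized on a 20-point difference in detection but tested with a log-link GEE; the stated 80% power is met on neither scale, and the usual log-ratio test is the less reliable one at a 5% rate

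*Protocol article*

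**What the plan says.** The abstract names the primary outcome: "Change in the detection rates of depression between intervention and control arms will be the primary outcome".

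The Sample size section starts by "considering a 5% detection rate of depression at primary care level" and "assuming a difference in detection rate by 20% between the intervention and control arm". It continues "Assuming an equal cluster size of 300, we will require 4 PHCs in each arm", then "Considering 20% attrition rate, intra-class correlation (ICC) as 0.1", and concludes "with 80% power, 5% alpha error for two-sided test, the minimum sample size required is 1200 adults per arm". Nothing in that section refers to a ratio.

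The Statistical methods section opens the comparison with "The difference in the detection and recovery rates between intervention and control arms" and says it will be "compared using generalised estimating equation (GEE) analysis with a log link and exchangeable correlation structure to adjust for cluster effects". The same sentence applies this model to risk factors for depression. The section names no identity link, risk-difference estimate, type of test (Wald or score) or small-sample correction.

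**The concern.** The sizing uses a difference of proportions, while the arm coefficient of a log-link model is a log risk ratio. Both have the same null hypothesis of equal rates, and the choice of scale often matters little. Here it can matter, because the control rate is low, the ICC is large relative to that rate, and there are four PHCs per arm. The standard error of a log ratio depends on relative variation. In the control arm the between-PHC coefficient of variation implied by the inputs is sqrt(0.1 × 0.95/0.05) = 1.38, to be estimated from four PHCs. The standard error of the difference depends on absolute variation, which is small at 5%.

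Two things are at stake: whether the stated power describes the planned test, and whether that test holds its 5% false-positive rate if usual-care detection is as low as assumed.

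**Working it through.** **Inputs (Sample size section).** Control rate p0 = 0.05; intervention rate p1 = 0.25; m = 300 per PHC; 4 PHCs per arm; ICC 0.1; two-sided 5%; 80% power; 20% attrition. The 20% is read as percentage points. A relative 20% (5% v 6%) would need more than 200,000 adults per arm, so it cannot be what was meant.

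**Step 1. The plan's own figure.** Under individual randomisation, the two-proportion formula with p̄ = 0.15 gives

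n = [1.96 × sqrt(2 × 0.15 × 0.85) + 0.842 × sqrt(0.05 × 0.95 + 0.25 × 0.75)]² / 0.20² ≈ 49 per arm.

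The design effect is 1 + 299 × 0.1 = 30.9, so 49 × 30.9 = 1514 per arm, or 1514/0.8 = 1893 with attrition. The stated 1200 is not reproduced with all the stated inputs. A one-sided test without attrition comes close: 39 × 30.9 = 1205.

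**Step 2. Large-sample power at 1200 per arm.** The effective size is 1200/30.9 = 38.8 per arm.

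- Difference: SE = sqrt((0.0475 + 0.1875)/38.8) = 0.0778; z = 0.20/0.0778 = 2.57; power = Φ(2.57 − 1.96) = 73%.
- Log ratio: SE = sqrt((0.95/0.05 + 0.75/0.25)/38.8) = sqrt(22/38.8) = 0.753; z = ln 5/0.753 = 2.14; power = Φ(2.14 − 1.96) = 57%.

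The control arm supplies 19/22 = 86% of the log-ratio variance but only 0.0475/0.235 = 20% of the variance of the difference. With a noncentral t on 6 df (8 PHCs minus 2), the powers are about 58% and 44%. With 240 completers per PHC the large-sample values are unchanged to the nearest point (73% and 57%).

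PHCs per arm for 80% power, large-sample:

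- Difference: 7.85 × (30.9/300) × 0.235/0.04 = 4.75.
- Log ratio: 7.85 × (30.9/300) × 22/(ln 5)² = 6.9.

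**Step 3. Simulation.** 200,000 trials per setting, 4 PHCs of 300 per arm, beta-distributed PHC rates with ICC 0.1. With equal PHC sizes the GEE estimates are the arm means of the PHC proportions, and the closed-form robust statistics matched fitted exchangeable GEEs on test data. *Corrected* means the robust variance multiplied by 4/3 and referred to t on 6 df. *Size-matched* means each statistic is compared with its own simulated 5% critical value at the given common null rate.

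| Common null rate | False positives, corrected: difference / log ratio | Size-matched power at 5% v 25%: difference / log ratio |
|---|---|---|
| 5% | 3% / 10% | 70% / 42% |
| 10% | 4% / 7% | 65% / 51% |
| 15% | 4–5% / 6% | 63% / 55% |
| 25% | 5% / 5% | 61% / 57% |

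Nominal power at 5% v 25%, without size-matching:

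- Corrected, t on 6 df: 61% (difference) v 59% (log ratio).
- Uncorrected robust z: 84% v 80%. At a 5% null rate these uncorrected tests have false-positive rates of about 12% and 23%.

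**Step 4. Sensitivity.** With logit-normal PHC rates, the corrected false-positive rates at a 5% null are again about 3% and 10%. The size-matched loss is about 20, 11, 6 and 0 points at null rates of 5, 10, 15 and 25%. The corrected nominal power is 65% for the difference and 68% for the log ratio.

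**The case against.** Much of the case on the other side stands.

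- **The size-matched loss is not the loss of a test the team would run.** It needs simulated critical values, a null rate and a distribution of PHC rates, and the protocol gives none of these. A reader might infer from the 5% null that the log link costs some 28 points of power at the plan's own inputs. The documents do not support that as a general statement. It is the top of a range that falls to about 3 points (beta) or nil (logit-normal) at a 25% null, and the nominal powers of the runnable tests are within a few points of each other. The practical defect is mainly excess false positives.
- **The loss belongs to the Wald log-ratio statistic, not to the link as such.** A GEE score test does not depend on the link and had the same size-matched power as the difference. The protocol does not say which test is used, and a statistical analysis plan may. That the test will be Wald is an inference from the usual software output.
- **It is tempting to say the stated power is right for the difference and wrong only for the ratio.** It is not: the difference reaches 73%. Too few PHCs is a separate and larger cause of the shortfall, and changing the link does not cure it.
- **Nor would the percentage-point difference be lost.** Statistical methods describes categorical data by percentages, and a difference can be derived from an arm-only log-link model.

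Reporting a risk ratio after sizing on two proportions is common and is not a contradiction in itself. What survives is that the stated power does not describe the planned model, and that the usual test from that model is poorly calibrated at the detection rate the trial assumes.

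**Conclusion.** The point holds as a mismatch between the sizing and the planned model. By the usual large-sample formula, power is about 57% for the log ratio and 73% for the difference, against a stated 80%. This 16-point gap rests only on the Sample size inputs, read as 5% v 25% with equal PHC sizes.

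The reliability finding is narrower. With eight PHCs and a common rate near 5%, a corrected Wald log-ratio test has a simulated false-positive rate of about 10%, against 3% for the difference. This assumes a Wald test and no site effect. It is similar for beta and logit-normal PHC rates, and it fades as the common rate rises. The size-matched power loss is roughly 3 to 28 points with beta-distributed rates and 0 to 20 with logit-normal rates, so no single figure should be quoted for it.

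It should be corrected, since the stated power is a property the design does not have. It ranks after the number of PHCs and the small-sample handling.

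**What to change.** **Statistical methods.** Base the primary detection test on the risk difference (identity-link GEE with exchangeable correlation or, with equal PHC sizes, the difference in mean PHC proportions), or on a link-invariant GEE score test. State the small-sample handling. Report the risk ratio alongside, and keep the log link for the risk-factor models.

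**Sample size.** Restate the power for whichever test is primary: about 73% for the difference or 57% for the log ratio by the large-sample formula, or about 58% or 44% with t on 6 df. This discloses the shortfall; it does not remove it.

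**Cost.** A few sentences and a small change of code, with no extra participants or data. If the difference is chosen, the ratio is no longer the tested quantity, which is partly a choice of estimand. An identity link can give fitted values outside 0 to 1 if many covariates are added, so the primary model should be kept sparse.
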